**Protein, Glucose, Ketone, Occult Blood, Bacteria, etc.**

■ **Laboratory test 2:** A pelvic X-ray will be taken to confirm the presence of osteitis in order to select subjects and confirm that they meet the exclusion criteria.

■ **Laboratory tests3 :** Bacteriologic identification and histologic examination will be performed immediately before study treatment (D1), immediately after study treatment (D29), and at long-term follow-up after study treatment (D210) to observe the change process.

✓ **Bacterial identification test:** Bacterial identification test performed on a tissue sample. Test results take about 7 days.

✓ **Histologic examination:** The process of tissue changes in the wound is identified through histologic examination and immunochemical examination (IL-1, 4, 6, 10,

13, TNF-a, TGF-b, MMP-1, 2, TIMP, Colla1, 3, etc.

Understand the recovery process.

- ✓ **This test is performed using a 3- to 4-mm punch biopsy and is only performed on individuals who have given their consent.**

- ✓ **The test is necessary for the treatment of pressure ulcers, which are invasive or chronic infectious wounds,** and the test does not contribute to **delayed wound healing or harm to the patient.** The following example shows the wound healing process of a patient with a pressure ulcer who had a bacterial culture and biopsy performed, demonstrating that the test was not harmful to the patient's wound healing.

[figure not shown]

**Figure 17.** Example of spontaneous wound healing in a pressure ulcer patient with bacterial culture and histology.

- **Confirmation of adverse events:** Information on adverse events is taught to the subjects to report voluntarily from time to time, and the investigator confirms the occurrence of adverse events through questioning. In the event of an adverse event, the date of onset and disappearance, the extent and consequences of the adverse event, the measures taken in relation to the irradiation and the causal relationship with the irradiation, the name of the suspected drug or treatment other than irradiation, and whether and how the adverse event was treated are recorded in detail in the case record sheet.
- **Expected adverse events in this study** (based on a 2014 Cochrane review by Chen C. et al)
  - Possible side effects include increased exudate, bacterial growth, wound bleeding, and tissue necrosis due to stimulation of the inflammatory response.

- A 2014 Cochrane review by Chen C. et al. found that photobiologic therapy can also cause side effects such as pain, microbleeds, and redness.

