Pressure ulcers are a classic example of a chronic wound with a sustained inflammatory response, and while **recovery** time varies depending on the extent and depth of the tissue lost, **1-3 months for mild cases** and at **least 6 months for moderate or more severe cases.**

**~1 year or more.** Recovery, however, is not guaranteed, but can be achieved if the direct causative pressure is relieved and the indirect causative factors, such as internal medicine management and nutrition, and ongoing wound care, that have not been addressed, leading to sustained pressure, are addressed.

[figure not shown]

**Figure 3.** NPUAP Pressure Ulcer Classification

[figure not shown]

**Figure 4.** Multifactorial causes of pressure ulcers

This **multifactorial, high societal cost of pressure** ulcers is a **global issue, and** medical experts from the United States, Europe, and the Pacific Rim (National Pressure Injury Advisory Panel - European Pressure Ulcer Advisory Panel - Pan Pacific Pressure Injury Alliance) have published three international guidelines on pressure ulcers since 2009 (first edition 2009, revised 2014, 2019). The guidelines state that the **best treatment for pressure ulcers is prevention** and **emphasize the importance of positioning**. Depending on the study, up to 95% of pressure ulcers are preventable.

However, once skin necrosis has occurred, it can be accompanied by infection, so limbectomy should be performed first. After limbectomy, the defect can be surgically repaired with flaps, but if general anesthesia cannot be performed, **conservative treatment is the only option**. In this case, it is **very important to control inflammation and promote the wound healing process**. To date, many wound coverings have been developed, and wound healing can be facilitated by choosing the right antiseptic for the condition of the wound. However, each treatment has its own limitations and there is no single method for the conservative treatment of pressure ulcers.

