#### **10.3.5 Visit 15 (D210 ± 2 days)**

Medical examination and measurement of vital signs.

Measurement of erythema, Braden scale, and NRS.

Performed mycobacterial culture and histologic examination.

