**13.2 Secondary validity measure: immunochemical markers on tissue examination**

- Pro-inflammatory cytokine (IL-6) / Anti-inflammatory cytokine (IL-10) ratio was obtained and the progression to the proliferative phase was analyzed by comparing the control and experimental groups after 0 and 4 weeks.
- Immunochemical markers are measured in a laboratory by a researcher through RNA sequencing, with final confirmation by the Principal Investigator.

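### The D210 punch biopsy comes after most mild ulcers are expected to have closed, serves no endpoint named in the protocol, and has no scheduled adverse-event check at or after it.

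*Protocol*

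**What the plan says.** Section 10.2 (Laboratory tests 3) times culture and histology just before treatment (D1), just after it (D29), and "at long-term follow-up after study treatment (D210) to observe the change process". It adds: "This test is performed using a 3- to 4-mm punch biopsy and is only performed on individuals who have given their consent". The 10.1 table marks the same tests at Visits 2 (D1), 14 and 15, and the Visit 15 list in 10.3.5 includes "Performed mycobacterial culture and histologic examination". None of these places makes the D210 sample depend on the state of the wound.

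On healing, section 5.2 gives "1-3 months for mild cases", and section 8 repeats that range. Both add that closure is not certain. Section 8 justifies long follow-up by a maturation period of up to six months after healing.

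On use of the tissue, section 13.2 analyses the IL-6/IL-10 ratio by "comparing the control and experimental groups after 0 and 4 weeks". The Protocol Summary gives the same two time points, and the primary objective in 5.1 is also set at four weeks.

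On justification, section 10.2 calls the test necessary for treating pressure ulcers, "which are invasive or chronic infectious wounds". It supports harmlessness with one illustrated ulcer patient (Figure 17), "demonstrating that the test was not harmful to the patient's wound healing".

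On safety, the adverse-event row in 10.1 is marked for Weeks 1 to 4 and Visit 14 and is blank at Visit 15. Section 10.3.4 lists an adverse-event check and 10.3.5 does not. Section 9.2.1 promises periodic adverse-event determination during follow-up, and 14.4 promises follow-up to six months beyond the end of the study.

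**The concern.** A study biopsy is a burden that the information from it should justify. At D1 and D29 the sample feeds the secondary endpoint and is taken from, or close in time to, an open ulcer. At D210 neither need be true. In a subject whose ulcer has closed, the sample would probably be a new small wound at or near a former pressure-ulcer site, in a patient enrolled because of susceptibility to pressure damage. The protocol offers no reasoning for that situation.

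The sample also falls at the last visit. If the biopsy site failed to heal, or the culture called for action, no scheduled contact would pick it up. At stake are subject burden and the capture of harm, not the validity of the main comparison.

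**Working it through.** **The plan's own figure.** Section 7.3 aims for 16 per arm with 15% dropout: 16 / (1 − 0.15) = 18.8, rounded up to 19 per arm, or 38 in total. This reproduces the stated size, and the point does not depend on it.

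**Exposure at D210.** The ceiling is 38. After 15% dropout, 38 × 0.85 = 32.3, about 32. Refusals lower this further; the protocol gives no refusal rate for biopsy.

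**Time since expected closure.** Inputs: 1-3 months (5.2 and 8), D210 (10.1), 30.44 days per month, counting from D0.
- Upper end: 3 × 30.44 = 91 days; 210 − 91 = 119 days, or 3.9 months before the biopsy.
- Lower end: 1 × 30.44 = 30 days; 210 − 30 = 180 days, or 5.9 months before the biopsy.

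So the expected closure of a mild ulcer lies about 4 to 6 months before the D210 sample.

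**Is the tissue used?** The objective (5.1), the summary's analysis and section 13.2 all stop at week 4. D210 appears only in the scheduling text, with the aim of observing change.

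**Does the justification reach D210?** Both the necessity statement and the single supporting example in 10.2 concern a pressure ulcer as a wound. Neither speaks to sampling closed skin, and no passage says where to sample once the ulcer has closed. The expected side effects in 10.2, 11.1 and 18 are not attributed to the biopsy; section 18 mentions biopsies only as a test that the study pays for.

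**What follows the sample?** Culture takes about 7 days (10.2): 210 + 7 = D217, or D215 to D219 with the ±2-day window. No visit remains by then. The six months in 14.4 can be read in two ways:
- From end of treatment (D29): 6 × 30.44 = 183 days; 29 + 183 = D212, which is Visit 15 within its window. Nothing follows the biopsy.
- From the last visit (D210): 210 + 183 = D393, about 12.9 months in. This covers the biopsy, but no visit or contact is scheduled to deliver it.

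Under either reading, the schedule in 10.1 and 10.3.5 and the promises in 9.2.1 and 14.4 do not fit together.

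**The case against.** The strongest defence is that D210 suits a descriptive purpose. Closure at 1-3 months plus six months of maturation ends at about 7 × 30.44 = D213 to 9 × 30.44 = D274, so D210 falls within that period or at its edge. The panel in 10.2 includes TGF-b, MMP, TIMP and collagen markers, which an examination cannot measure. Section 5.2 faults earlier work for reporting only final outcomes, and the trial is labelled exploratory. A statistical analysis plan, not shown here, could describe D210 tissue. All of this stands: the sample has a stated descriptive aim, and the supportable criticism is that this protocol names no objective or endpoint for it.

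On safety, subjects are taught to report events themselves (10.2), findings at each examination that meet the definition are recorded as adverse events (10.2), and section 19.3 requires care during and after the study. This also stands. None of it, however, is a scheduled check on a biopsy site after Visit 15.

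Biopsy is done only with consent. That limits exposure but does not supply a use for the sample.

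**Conclusion.** The point holds in a bounded form. The protocol schedules an invasive sample at D210 whatever the state of the wound, about 4 to 6 months after most mild ulcers are expected to have closed. It names no endpoint for the sample, gives no justification that covers healed skin, and schedules no adverse-event check at or after it. At most 38 subjects are affected, about 32 after planned dropout, fewer with refusals. The calculation assumes that the 1-3 month course runs from enrolment and that the Visit 15 culture and histology are the punch-biopsy tests of 10.2.

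A reader might infer more, and the documents do not support it:
- That every ulcer has closed by D210. Sections 5.2 and 8 say healing is not assured.
- That safety follow-up is wholly absent. Sections 9.2.1 and 14.4 promise it; the defect is an unreconciled conflict with the schedule.
- That each biopsy leaves a full-thickness defect in the old ulcer site. Only the punch diameter is given; depth and the sampling site after closure are not.
- That a third biopsy deters consent to the first two. Nothing in the protocol bears on this.

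This is an inexpensive improvement to burden and harm capture. It changes neither the sample size nor the main result.

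**What to change.** In the 10.1 table, 10.2 (Laboratory tests 3) and 10.3.5, limit D210 culture and histology to subjects whose ulcer is still open, or remove them. Keep the Visit 15 examination, vital signs, erythema, Braden and pain scores. Reconcile the blank adverse-event cell in 10.1 and the list in 10.3.5 with 9.2.1 and 14.4: state from which date the six months run, and attach an adverse-event check that covers any biopsy still taken at D210, including its culture result.

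If the sponsor wants late histology in healed subjects, the protocol should state the objective, say who is sampled and where, and schedule that check.

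The cost is a short amendment. Descriptive late-maturation histology, the only tissue data after week 4, is lost or limited to unhealed ulcers; some procedure and laboratory cost is saved.

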### **10.3 Observational Test Method**

**10.3.1 Screening Visit (Visit 1, -D14 to D1):** Subjects selected to participate in this study will receive an explanation of the study and be assessed in the following order.

Explain the test process and obtain written consent from subjects before allowing them to participate in the test.

Subjects are corrected on their screening numbers in order.

- ③ Investigate the subject's demographics and medical history.
- ④ For women of childbearing age, perform a pregnancy test.

Perform a physical exam and vital signs.

- ⑥ Measurement of erythema, Braden scale, and NRS.
- ⑦ Blood tests, urinalysis, and pelvic X-ray.

#### **10.3.2 Visit 2 (D1 ± 2 days)**

Recheck the selection criteria and exclusion criteria before irradiation, then judge the suitability and assign the subject number.

Medical examination and measurement of vital signs

Measures area assessment, Braden scale, and NRS

- ④ Phototherapy performed.
  - ⑤ Performed bacterial identification and histologic examination
- Checked medical history and medications.
- ⑦ Check for adverse events.

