## 9 Clinical Trial Methods

### 9.1 Designing a clinical trial

For subjects who signed the informed consent form of their own volition, after conducting the necessary examinations and tests according to the protocol, reviewing the inclusion and exclusion criteria, and deeming them suitable for this study, educating them about the study schedule and methods. The subjects will be **irradiated with 4 wavelengths of LEDs at maximum power (5 levels,  mW/cm^2) for maximum time (25 minutes) at a distance of 15 cm from the pressure ulcer in the buttock area. LED irradiation is performed 3 times per week, with a medical examination and wound assessment at the end of each week's treatment. This is done for a total of 4 weeks.**

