| Medical exams
and
Vital signs                                               | ○            | ○                     | ○                     | ○                      | ○                       | ○           | ○           |
| Annulus and
Braden scale
side
正                                          | ○            | ○                     | ○                     | ○                      | ○                       | ○           | ○           |
| Measuring pain
scores                                                          | ○            | ○                     | ○                     | ○                      | ○                       | ○           | ○           |

|                                                                    |                       |                                                 |                       |                       |                       |                       |                       |
|--------------------------------------------------------------------|-----------------------|-------------------------------------------------|-----------------------|-----------------------|-----------------------|-----------------------|-----------------------|
| Laboratory tests1 (blood tests, urinalysis f)                      |  |                                                 |                       |                       |                       |  |                       |
| Laboratory tests2 (pelvic X-ray)                                   |  |                                                 |                       |                       |                       |                       |                       |
| Medical Device Applications                                        |                       |                            |  |  |  |  |                       |
| Laboratory tests3 (fungal culture, tissue biopsy)                  |                       | 
(Proceed with D1 only) |                       |                       |                       |  |  |

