#### **10.3.4 Visit 14 (D29 ± 2 days)**

Medical examination and measurement of vital signs.

Measures area assessment, Braden Scale, and NRS

Performed blood tests, urinalysis, mycology tests, and biopsies.

- ④ Checked medical history, medications.
- ⑤ Check for adverse events.

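### Sections 10.2 and 10.3.2 give opposite orders for the D1 biopsy and first irradiation, and the schedule marks a D29 device application that the visit text omits, so the tissue samples are not clearly timed relative to treatment

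*Protocol*

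**What the plan says.** **Order on D1.** Protocol Section 10.2 (Laboratory tests 3) sets the times for bacterial identification and histology as "immediately before study treatment (D1), immediately after study treatment (D29), and at long-term follow-up after study treatment (D210". The Visit 2 list in Section 10.3.2 numbers its steps and gives "④ Phototherapy performed", followed by "⑤ Performed bacterial identification and histologic examination".

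**Device use on D29.** In the Section 10.1 timeline, the row "Medical Device Applications" is marked for each of the four treatment weeks and again at Visit 14 (D29), which sits under the monitoring columns. The Visit 14 text in Section 10.3.4 includes "Performed blood tests, urinalysis, mycology tests, and biopsies" and has no irradiation step. Section 9.1 says "LED irradiation is performed 3 times per week", for four weeks in total.

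**Use of the tissue.** Section 13.2 makes the IL-6/IL-10 ratio, compared between arms at 0 and 4 weeks, the secondary efficacy measure. Section 5.1 also names immunochemical markers in the primary objective. Section 10.2 limits the biopsy to subjects who consent to it.

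**The concern.** A week-0 marker serves as a baseline only if it is taken before the arms are treated differently. The protocol gives two opposite orders for the same sample. Site staff working down the Visit 2 list would take tissue that has just had a full session. The baseline would then be a post-randomisation measurement, and a change from it, or an adjustment for it, could absorb or exaggerate part of a device effect. Once light has been given, no pre-treatment sample can be recovered and no later analysis can replace it.

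The D29 mark raises a different question. The week-4 sample is meant to follow treatment, but the protocol does not settle how many sessions precede it or how long after the last session it is taken. Subjects handled under the schedule and under the visit text would contribute samples with different timing to the same endpoint.

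**Working it through.** **1. D1, side by side**

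| Source | Order on D1 |
|---|---|
| Section 10.2, Laboratory tests 3 | culture and biopsy, then treatment |
| Section 10.3.2, Visit 2 list | item 4 irradiation, then item 5 culture and biopsy |

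The two cannot both be followed. The wound assessment stands ahead of item 4 in the same list, so the primary wound-size baseline precedes light under either order.

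**2. Exposure before sampling if Section 10.3.2 is followed**

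Inputs: 25 minutes = 1,500 s; test output 90 mW/cm² (Section 9.3.2); sham output 12 mW/cm² (Section 9.3.6.2), stated elsewhere as 12 or less. The level 5 outputs in Section 6.1.6.1 sum to 8.4 + 12 + 30 + 40 = 90.4 mW/cm², in line with the nominal 90.

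- Test: 90 × 1,500 / 1,000 = 135 J/cm².
- Sham: 12 × 1,500 / 1,000 = 18 J/cm², an upper bound.

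**3. What this does to the comparison**

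Let one session shift the marker by a_T in the test arm and a_S in the sham arm at the time of sampling, and let Δ be the true between-arm difference in change from a pre-treatment baseline.

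- Difference in change as measured: Δ − (a_T − a_S).
- With baseline adjustment at slope b, the treatment estimate moves by −b(a_T − a_S).
- A comparison of week-4 values alone does not move.

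The protocol gives no value for a_T or a_S, and no sign. If neither arm shifts, or both shift equally, there is no bias.

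**4. Session count**

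- Section 9.1: 3 per week × 4 weeks = 12.
- Visits 2 to 13 (D1, 3, 5, 8, 10, 12, 15, 17, 19, 22, 24, 26): 12 visits, each with irradiation in Sections 10.3.2 and 10.3.3. The text is consistent at 12.
- Section 10.1 with the D29 mark: 12 + 1 = 13, which is 1/12 = 8.3% more sessions.

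**5. Interval from last irradiation to the week-4 biopsy**

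- Visit text: 29 − 26 = 3 days, nominal.
- D29 mark followed: 0 days, with the order of irradiation and biopsy that day not stated.
- With the ±2-day windows applied to the visit text: from (29 − 2) − (26 + 2) = −1 to (29 + 2) − (26 − 2) = 7 days. The windows overlap, so even without the D29 mark the interval is only loosely held.

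**The case against.** The best reply is that Section 10.2 states an explicit timing rule, while the Visit 2 list is a checklist. Only the screening list in Section 10.3.1 says that its steps are done in order. The Visit 2 list also puts the medication check after phototherapy, although light-related medication is an exclusion criterion and eligibility is to be rechecked before irradiation. That suggests the list is not a strict sequence. This stands in part: a post-light sample follows only if staff take Section 10.3.2 as chronological over Section 10.2. But the steps are numbered, and the list opens with what must be done before irradiation, so working down it is a reasonable reading.

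The affected scope is narrow. The primary wound measure is untouched, the biopsy is optional, and culture is not a listed efficacy endpoint. All of this stands.

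A reader might infer that both tissue time points are contaminated by treatment. The documents do not support that for D29. That sample is post-treatment by design, a further session would apply to both arms, and no text places irradiation before biopsy that day.

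A reader might also infer that the device effect is diluted by some fraction. No acute-effect figure is given. Section 11.1 lists side effects from stimulation of the inflammatory response, so a session could raise the baseline ratio in the test arm and enlarge the apparent fall.

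**Conclusion.** Two internal contradictions stand in the current text.

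- **D1.** If Section 10.3.2 is followed, the week-0 IL-6/IL-10 ratio is taken after one arm-specific session (about 135 against at most 18 J/cm²) and is not a true pre-treatment baseline. This is conditional on the list being used as a sequence. The size and direction of any bias cannot be derived.
- **D29.** The session count is 12 or 13, and the nominal interval from last irradiation to the week-4 biopsy is 3 days or 0 days. The defect is undefined timing, not contamination.

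The consequences are confined to the tissue markers and the D1 culture, in an exploratory trial that targets 16 evaluable subjects per arm with biopsy only where consented. The point is still worth correcting because a lost pre-treatment sample cannot be recovered.

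**What to change.** In Section 10.3.2, list the culture and biopsy step before the phototherapy step so that it agrees with Section 10.2. Reconcile Sections 9.1, 10.1 and 10.3.4 on whether the device is applied at Visit 14, so that one session count, and one timing of the week-4 sample relative to the last irradiation, stand throughout. Which count is intended is for the sponsor and the investigator to settle.

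The cost is one reordered list and one corrected table cell or visit text. Neither the D1 reordering nor the reconciliation adds a procedure, and the sample size is unchanged.
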